## 1. Introduction

Community-acquired pneumonia (CAP) is a common and serious illness. In developed countries it is the most important cause of death due to an infectious disease and in the Netherlands it is the fourth leading cause of death overall.

In CAP caused by bacteria prompt initiation of antibiotic therapy is recommended, since a delay might be associated with increased mortality. The optimal duration of antibiotic therapy in bacterial CAP remains unknown. Most likely, it varies from patient to patient.

Current guidelines recommend treatment duration of 7-21 days, depending on illness severity and type of pathogen. However, adherence to guidelines is variable and physicians tend to treat longer, especially in patients with comorbidities and patients with severe CAP. Duration of treatment can be guided by clinical signs, but interpretation of the clinical response lacks standardization and is prone to interobserver variability.

A new approach to estimate the presence of an infection and response to treatment is the use of biomarkers. Circulating levels of calcitonin precursors, including procalcitonin are elevated in bacterial infections. Procalcitonin can follow either a classic hormonal expression pathway or in the presence of an infection, a cytokine-like expression pathway.

The release of procalcitonin during infection can be induced either directly by microbial toxins such as endotoxin and indirectly by humoral factors such as IL-1 $\beta$ , TNF- $\alpha$  and IL-6 or the cell-mediated host response.

Several studies have shown procalcitonin can be used as a marker for bacterial lower respiratory infections and CAP. Some studies demonstrate procalcitonin can be used effectively and safely as a marker to initiate or discontinue treatment with antibiotics. However only one of these trials focuses on patients with CAP admitted to hospital. One of our objectives is to validate the procalcitonin based treatment strategy mentioned by Christ Crain et al. and Long et al.

A different way to assess the presence of (bacterial) infection is measuring the blood level of C-Reactive Protein (CRP). An elevated CRP correlates only with (systemic) inflammation and not per se infection. Several studies have attempted to use CRP as a marker in lower respiratory tract infections and CAP in a primary care setting. Over the years several reviews have questioned the use of CRP in patients with community acquired pneumonia/lower respiratory tract infections as a marker to initiate or withhold antibiotic treatment. There is however evidence that supports the use of consecutive measurements of CRP in follow up of antibiotic treatment in CAP. Several studies showed that a delayed normalisation of CRP within the first 3–7 days of follow-up is suggestive of inappropriate antibiotic therapy and eventually treatment failure.

Using the database from the CAPISCE study we retrospectively derived a CRP based treatment strategy which we believe can be used just as effectively as the PCT based strategy to discontinue antibiotic treatment in patients with CAP admitted to hospital.

Our main goal is to determine whether the CRP and PCT guided strategies can be used to safely and effectively reduce the duration of antibiotic treatment in patients with CAP admitted to hospital. The rationale and criteria of the two different strategies is outlined in chapter 4.4

## **2. Objectives**

### **2.1 Primary objective(s)**

The primary objective of this study is to determine whether a CRP guided and PCT guided treatment strategy (strategies mentioned below) can be used to safely and effectively reduce the duration of antibiotic treatment as compared to common clinical practice in patients with CAP requiring hospitalisation.

The diagnosis CAP will be made if a non-hospitalized person presents with one or more symptoms associated with a lower respiratory tract infection **and** a new infiltrate on the chest radiograph. These symptoms are: temperature greater than 38°C (100.4°F); cough with or without sputum; hemoptysis; pleuritic chest pain; dyspnea; malaise or fatigue; myalgia; gastro-intestinal symptoms; rales, rhonchi or wheezing; egophony or bronchial breath sounds.

The 3 different treatment strategies are as follows:

1. Treatment according to common practice: often a 7 day course of antibiotics.
2. Treatment with antibiotics for at least 3 days according to current guidelines, with extension of antibiotic treatment according to procalcitonin levels. Antibiotic treatment will be discontinued if the procalcitonin level is below 0.25 mcg/L **or** shows a reduction to 10% of the initial value.
3. Treatment for 3 days according to current guidelines, with extension of antibiotic treatment according to CRP levels. Antibiotic treatment will be discontinued if the value is below 100 mg/L **and** shows a reduction to 50% of the initial value.

### **2.2 Secondary objective(s)**

The secondary objectives of this study are to assess the length of hospital stay, clinical response, 30-day mortality, time to clinical stability and relapse rate within 30 days. A relapse is defined as new or worsening symptoms indicative of pneumonia after initial improvement on therapy. Furthermore several biomarkers and genetic polymorphisms for corticosteroid-receptors will be assessed at the end of the study.

## **3. Study design**

This study will be set up as a Randomised Controlled Trial with a parallel design, patients will be randomly allocated to one of 3 treatment groups. No blinding will be performed, since treating physicians will have to make a decision to continue or withhold treatment based on laboratory evaluations. In order to make the right decision they will have to know whether or not the patient is receiving antibiotics.

Patients will be included at hospital admission and the follow up period is 1 month. The control group will consist of patients getting treated according to common clinical practice.

Patients will be admitted to hospital and receive therapy according to the study protocol. They will be discharged from the hospital when their medical condition and social situation is stable. If patients are discharged and still using antibiotics, blood tests will be performed daily in the participating centre and the researcher will contact the patients by phone to inform them whether or not antibiotic treatment can be discontinued. After discharge the patient will be evaluated at an outpatient visit on day 30. In case of any event an interim visit will be scheduled. If for some reason a patient fails to perform an outpatient blood test, antibiotics will be continued until the next blood test or for a total of 7 days and the reason for failure will be documented.

This study will be conducted in the Medical Centre Alkmaar, the Isala clinics in Zwolle and the Slotervaart hospital in Amsterdam.

## 4. Study population

### 4.1 Population

A total of 468 patients will be enrolled into this study and will be divided into three equally large groups.

### 4.2 Inclusion criteria

Male and female patients with a diagnosis of CAP and all criteria listed below:

1. Age 18 or above, no upper age limit will be employed.
2. Patients must require hospitalisation.
3. Clinical presentation of an acute illness with one or more of the following symptoms:
  - a. Temperature  $\geq 38.0^{\circ}\text{C}$  ( $100.4^{\circ}\text{F}$ )
  - b. Dyspnoea
  - c. Cough (with or without expectoration of sputum)
  - d. Chest pain
  - e. Malaise or fatigue
  - f. Myalgia
  - g. Gastro-intestinal symptoms
  - h. Rales, rhonchi or wheezing
  - i. Egophony or bronchial breath sounds
  - j. Hemoptysis.
4. New consolidation(s) on the chest radiograph.
5. Written informed consent obtained.
6. (Pre-event) Life expectancy > 30 days.

### 4.3 Exclusion criteria

Subjects presenting with any of the following will not be included in the study:

1. Severe immunosuppression (HIV infection, chemotherapy).
2. Active neoplastic disease.
3. Obstruction pneumonia (e.g. from lung cancer).
4. Aspiration pneumonia.
5. Pneumonia that developed within 8 days after hospital discharge.
6. Unable and/or unlikely to comprehend and/or follow the protocol.
7. Pregnant and/or lactating women.

### 4.4 Sample size calculation.

The objective of this study is to assess the efficacy of two different treatment regimens as compared to current general practice. The primary analysis will be the comparison of the duration of antibiotic treatment of the CRP-guided treatment group compared to common practice and of the PCT-guided treatment group compared to common practice in the intent-to-treat (ITT) population. A per-protocol analysis will be performed as well.

We used the criteria mentioned above for CRP and PCT (procalcitonin level below 0.25 mcg/L **or** a reduction to 10% of the initial value; CRP below 100 mg/L **and** a reduction to 50% of the initial value) to retrospectively perform an analysis on the database from the CAPISCE trial to predict a mean and a standard deviation of antibiotic treatment for both groups in order to perform the power analysis. We then retrospectively selected 170 cases from the CAP-START trial to derive a mean and standard deviation for the common clinical practice group. The results of all groups are listed below:

| Duration of theoretical antibiotic treatment in the CRP guided group |     |         |         |        |                |
|----------------------------------------------------------------------|-----|---------|---------|--------|----------------|
|                                                                      | N   | Minimum | Maximum | Mean   | Std. Deviation |
| crpdag                                                               | 196 | 1,00    | 14,00   | 5,1327 | 3,61518        |

| Duration of theoretical antibiotic treatment in the PCT guided group |     |         |         |        |                |
|-----------------------------------------------------------------------------|-----|---------|---------|--------|----------------|
|                                                                             | N   | Minimum | Maximum | Mean   | Std. Deviation |
| pctdag                                                                      | 173 | 1,00    | 14,00   | 6,2832 | 4,80257        |

| Duration of antibiotic treatment in the Common Clinical Practice group |     |         |         |        |                |
|-------------------------------------------------------------------------------|-----|---------|---------|--------|----------------|
|                                                                               | N   | Minimum | Maximum | Mean   | Std. Deviation |
| pctdag                                                                        | 170 | 0,00    | 42,00   | 8,7588 | 5,87499        |

We assume a mean difference of 2 days of antibiotic treatment to be clinically relevant. The results will be evaluated for a normal distribution using the kolmogorov-smirnov test. If they are normally distributed an ANOVA will be performed, with the addition of a Tukey-HSD test. If they are not normally distributed a Kruskal-Wallis test will be performed with the addition of separate Mann-Whitney U tests as post-hoc tests. The significance of these separate Mann-Whitney U tests will be corrected for multiple testing using the Bonferroni Holm method.

Using the means and standard deviations mentioned above, with an alpha of 0.025 (corrected for multiple testing using the Bonferroni Holm method) and a  $\beta$  of 0.20 this would require a total of 139 patients per group if the results are normally distributed and 146 patients per group if they aren't. A total of 148 patients per group will be included, to account for loss to follow-up, deaths etc. Which amounts to a total of 468 patients. Calculation was done by using the program G-power.

## **5. Treatment of subjects**

### **5.1 Days 1,2 and 3 – all groups**

All patients will receive treatment with broad-spectrum antibiotics for the first 3 days, which may be switched to small-spectrum antibiotics if a causative agent is found. This is in line with current guidelines.

### **5.2 Days 4 and after – common clinical practice group**

The patients in the common clinical practice group will receive antibiotics for a total of 7 days if no complications occur. Total treatment duration may be lengthened by the treating physician. The researcher will document the reason for this choice when this occurs.

### **5.3 Days 4 and after – PCT guided group**

Each day a blood test will be performed assessing the PCT level in the blood. If this shows a procalcitonin level below 0.25 mcg/L **or** a reduction to 10% of the initial value treatment will be discontinued. After the decision to discontinue treatment is made no further blood tests will be performed unless the patient has worsening symptoms.

### **5.4 Days 4 and after – CRP guided group**

Each day a blood test will be performed assessing the CRP level in the blood. If this shows a CRP below 100 mg/L **and** a reduction to 50% of the initial value treatment will be discontinued. After the decision to discontinue treatment is made no further blood tests will be performed unless the patient has worsening symptoms.

## **6. Methods**

### **6.1 Study parameters**

#### **6.1.1 Main study parameter**

The primary objective of this study is to determine whether the CRP and PCT strategies can be used to safely and effectively reduce the duration of antibiotic treatment in patients with CAP requiring hospitalisation.

### **6.1.2 Secondary study parameters**

The secondary objectives of this study are to assess the length of hospital stay, clinical response, 30-day mortality, time to clinical stability and relapse rate within 30 days. A relapse is defined as new or worsening symptoms indicative of pneumonia after initial improvement on therapy. Furthermore several biomarkers and genetic polymorphisms for corticosteroid-receptors will be assessed at the end of the study.

## **6.2 Randomisation and treatment allocation**

Randomisation will be done by using block-randomisation with a block size of 30 patients, which amounts to a total of 15 blocks of 30 patients and 1 block of 18 patients. The allocation ratio in each block will be 1:1:1. So each block will contain 10 patients getting treated according to Common Clinical Practice, 10 patients getting treated according to the CRP guided strategy and 10 patients getting treated according to the PCT guided strategy. The last block will contain 6 patients in each treatment group.

Each centre will start with a single block, upon completion they will be assigned the next available block. For example if centre A starts with block 1 and centre B starts with block 2, the centre who includes the first 30 patients will be assigned block 3. The main-investigator will be responsible for maintaining this list and appointing blocks to each centre.

No stratification will be performed, since there are no known or expected variables to warrant stratification.

Randomisation will be done by using a validated internet based randomisation strategy which can be found at [sealedenvelope.com](http://sealedenvelope.com).

Once a number is assigned to a patient, the investigator will open the treatment regimen assignment and the subject will receive treatment according to the assigned strategy.

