## **8.2 Randomisation method**

Randomisation will be done by using block-randomisation with a block size of 30 patients, which amounts to a total of 15 blocks of 30 patients and 1 block of 18 patients. The allocation ratio in each block will be 1:1:1. So each block will contain 10 patients getting treated according to Common Clinical Practice, 10 patients getting treated according to the CRP guided strategy and 10 patients getting treated according to the PCT guided strategy. The last block will contain 6 patients in each treatment group.

Each centre will start with a single block, upon completion they will be assigned the next available block. For example if centre A starts with block 1 and centre B starts with block 2, the centre who includes the first 30 patients will be assigned block 3. The main-investigator will be responsible for maintaining this list and appointing blocks to each centre.

No stratification will be performed, since there are no known or expected variables to warrant stratification.

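### A fixed, published block of 30, worked through centre by centre in an open trial, makes about 5% of allocations knowable in advance at block ends

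*Protocol*

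**What the plan says.** Protocol section 6.2, largely repeated in 8.2, fixes four things.

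- **Size.** "Randomisation will be done by using block-randomisation with a block size of 30 patients". The layout is given as fifteen full blocks and one short block of 18.
- **Content.** "The allocation ratio in each block will be 1:1:1", so each full block holds ten patients per arm. For the short block, "The last block will contain 6 patients in each treatment group".
- **Use by centre.** "Each centre will start with a single block, upon completion they will be assigned the next available block".
- **Administration.** "The main-investigator will be responsible for maintaining this list and appointing blocks to each centre".

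Section 3 makes the trial open: "No blinding will be performed, since treating physicians will have to make a decision to continue or withhold treatment based on laboratory evaluations". Section 9.2 has the attending physician or the investigator approach patients at admission. Section 6.2 also names an internet-based randomisation service and has the investigator open the assignment after a patient number has been given. Section 6.4.1 lists the eligibility check and consent before randomisation. The protocol does not provide for varied block lengths or for keeping the block size from recruiting staff.

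**The concern.** Blocking is meant to balance the arms without letting anyone foresee the next assignment. Here a centre has everything needed to work out what is left in its current block: the length, the exact content, the fact that it has the block to itself, and open knowledge of every earlier assignment. Once two arms have used all their places, the remaining assignments are known before the next patient is approached.

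The people who can make this deduction also recruit, and recruitment leaves room for judgement. Exclusion criterion 6 in section 4.3 concerns whether a patient is likely to understand and follow the protocol, and the decision to approach someone comes before consent. The primary outcome, duration of antibiotic treatment, is plausibly related to severity and partly depends on the physician: section 5.2 lets the treating physician extend the control course, and section 6.4.3 makes stopping in the guided arms conditional on clinical improvement. If sicker patients were held back when a guided arm was known to be next, or taken in when control was next, the difference in duration would be exaggerated.

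**Working it through.** **Inputs** (sections 6.2 and 8.2): 15 blocks of 30 with 10 per arm; 1 block of 18 with 6 per arm; three arms.

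**The plan's own layout.** 15 × 30 + 18 = 468 patients, and 15 × 10 + 6 = 156 per arm. Both agree with section 8.1.

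**Fully determined allocations.** In a block with k places per arm, the last j allocations all fall in one arm with probability 3 × C(k, j) / C(3k, j). When they do, each of those j assignments is known beforehand. The expected number of determined allocations per block is therefore the sum of this probability over j = 1 to k, which simplifies to 3k / (2k + 1).

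- Block of 30 (k = 10): 30 / 21 = 1.43, which is 4.8% of the block.
- Block of 18 (k = 6): 18 / 13 = 1.38.
- Whole trial: 15 × 1.4286 + 1.3846 = 22.8 of 468, or 4.9%.

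How this spreads over blocks of 30:

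- The 30th patient is always determined.
- The last two or more are determined in 3 × C(10,2) / C(30,2) = 135 / 435 = 31% of blocks.
- The last three or more are determined in 3 × C(10,3) / C(30,3) = 360 / 4060 = 8.9% of blocks.

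**Partial information.** By simulation of permuted blocks of 30, at least one arm is already used up for about 4.03 patients per block. Of these, 4.03 − 1.43 = 2.60 still have two arms open, so most are not foreseeable.

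**Best-guess rate.** Guessing the arm with most places left is right about 46% of the time over a block of 30, against 33% by chance. It rises from 52% at position 25 to 65% at position 29, and is 100% at position 30.

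**What varied lengths change.** The arm with most places left is the arm with fewest patients so far at that centre, because every completed block is balanced. That guess needs no knowledge of block length. In simulation it is right about 46% of the time both for a fixed length of 30 and for lengths drawn from 24, 27, 30, 33 and 36 that the recruiter does not know. Varied lengths therefore take away the certainty at block ends and leave the average guess rate as it is. Shorter fixed blocks would be worse: at size 6, 1.2 of 6 allocations (20%) are determined and the guess rate is 56%.

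**The case against.** The strongest reply is that the exposure is small and concealment is otherwise reasonable. A block of 30 is long, the sequence comes from a web service, eligibility and consent precede randomisation, and the assignment is opened only after a patient number is given. To exploit the block end, someone must keep a full tally of the centre's allocations, and recruitment need not lie with one person. In the guided arms, duration depends largely on fixed laboratory thresholds.

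Much of this stands. It makes 4.9% an upper bound and limits the bias to be expected. It does not remove the mechanism. Hiding the sequence does not stop deduction from a published total and open past assignments, and the choice of whom to approach is made before consent. With three centres, each on one block at a time, a tally is not hard to keep.

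Three stronger readings are tempting, and the documents do not support them.

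- A reader might infer that the main investigator holds the allocation sequence. The list in section 6.2 follows directly on the example of which centre receives which block, so it reads as the block-to-centre register. Nothing says that the main investigator sees the sequence.
- A reader might infer that no analysis could repair the resulting bias. That is too absolute: CURB-65 is recorded at baseline (6.4.1, 8.4.2) and correction for confounders is foreseen (8.4.3). Selection on unmeasured features is what would stay out of reach.
- A reader might conclude that centre must enter the primary analysis as a factor. That is a separate analysis question, and it does not fit the Kruskal-Wallis and Mann-Whitney route in section 8.1.

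**Conclusion.** The point holds in a narrow form. A fixed, published, centre-wise block in an open trial lets staff who keep count know on average 1.43 allocations per block of 30 with certainty, about 23 of 468 (4.9%) overall. The figure assumes that every earlier allocation at the centre is known to the recruiter, that the short block is recognised as such, and that all 16 blocks are completed.

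The defect is that the length is constant and disclosed; a length of 30 as such is not the problem. The 46% guess rate should not be counted as part of it, since it would be much the same under the remedy. The documents show an opportunity for selection and give no sign that it would be used. The change is worth making because it costs almost nothing and because patient selection cannot be undone after enrolment.

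**What to change.** 1. In sections 6.2 and 8.2, remove the block size, the content per block and the size of the last block from the text available to recruiting sites. State only that allocation is 1:1:1 in permuted blocks of varying length within centre, with details held in a restricted randomisation document.
2. Have the web service already named in 6.2 generate a separate list per centre with randomly varied lengths around the present size (24, 27, 30, 33 and 36 would be one such set). Do not disclose the set, and do not shorten the blocks.
3. Give block administration to someone who does not recruit. This is a matter of separating roles and implies nothing about what the main investigator can see.

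The order of eligibility, consent and randomisation in 6.4.1 can stay as it is.

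**Cost.** A setting in a service already in use and a short text change. Blocks may be unfinished when enrolment reaches 468, so arm totals may differ from 156 by a few patients.

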|                                                                               | N   | Minimum | Maximum | Mean   | Std. Deviation |
| dag                                                                           | 170 | 0,00    | 42,00   | 8,7588 | 5,87499        |

We assume a mean difference of 2 days of antibiotic treatment to be clinically relevant. The results will be evaluated for a normal distribution using the kolmogorov-smirnov test. If they are normally distributed an ANOVA will be performed, with the addition of a Tukey-HSD test. If they are not normally distributed a Kruskal-Wallis test will be performed with the addition of separate Mann-Whitney U tests as post-hoc tests. The significance of these separate Mann-Whitney U tests will be corrected for multiple testing using the Bonferroni Holm method.

Using the means and standard deviations mentioned above, with an alpha of 0.025 (corrected for multiple testing using the Bonferroni Holm method) and a  $\beta$  of 0.20 this would require a total of 139 patients per group if the results are normally distributed and 146 patients per group if they aren't. A total of 156 patients per group will be included, to account for loss to follow-up, deaths etc. Which amounts to a total of 468 patients. Calculation was done by using the program G-power.

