## **8.4 Methods of analysis**

### **8.4.1 General statistical considerations**

All data will be collected and analysed using SPSS statistics 20.

Statistical analysis will be performed on an intent-to-treat basis by an independent statistician. All continuous variables will be tested for normal distribution with the Kolmogorov-Smirnov test for normal distribution. The Student-t test will be used for normally distributed variables, the Mann-Whitney U test for not normally distributed variables and the  $\chi^2$  test for dichotomous variables. The software package SPSS 20 for Windows (IBM-SPSS Inc., Chicago, Illinois, USA) is available for statistical analysis. A value of  $p < 0.05$  will be considered significant.

All data will be collected and analysed using SPSS statistics 20.

Clinical response will be analysed by using the Kruskal wallis test.

Duration of treatment and in-hospital stay will be expressed as means with a 95% confidence interval. Sub-group analyses will be performed on patients with severe CAP according to the CURB criteria and patients with non-severe CAP.

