### **8.4.3 Efficacy analyses**

The primary efficacy analysis will be duration of antibiotic treatment.

The secondary efficacy analyses will be clinical response on day 30, length of hospital stay, time to clinical stability, relapse rate and overall mortality on day 30 and day 90.

Possible confounders (e.g. co-morbidities, type of pathogen etc.) will be assessed. Where appropriate a correction will be performed.

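### Blocks are dealt out centre by centre, so randomisation is in effect stratified by centre, but the protocol denies stratification and no specified analysis includes centre

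*Protocol*

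**What the plan says.** Sections 6.2 and 8.2 carry the same text. Blocks hold 30 patients, and "The allocation ratio in each block will be 1:1:1". The count is given as blocks "which amounts to a total of 15 blocks of 30 patients and 1 block of 18 patients". On who uses which block: "Each centre will start with a single block, upon completion they will be assigned the next available block". The same sections then state: "No stratification will be performed, since there are no known or expected variables to warrant stratification".

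Section 3 names the sites: "This study will be conducted in the Medical Centre Alkmaar, the Isala clinics in Zwolle and the Slotervaart hospital in Amsterdam".

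For the primary endpoint, sections 4.4 and 8.1 fix one-way tests. On the normal branch: "If they are normally distributed an ANOVA will be performed, with the addition of a Tukey-HSD test". On the other branch there is a Kruskal-Wallis test followed by Mann-Whitney tests with Holm correction. Sections 8.4.1 and 8.5 add t, Mann-Whitney and chi-square tests. Centre is named in none of them.

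**The concern.** A block that belongs to one centre and holds ten patients per arm forces the arms to be balanced within that centre. That is what stratifying by centre means, whatever the text calls it. The protocol therefore misdescribes its own design, and a reader who takes the statement at face value would see no reason to carry centre into the analysis.

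The consequence is statistical. When the arms are balanced within centre, differences between centres cancel out of the treatment comparison. A one-way test still counts those differences as noise, so its standard error is larger than the true one. Confidence intervals come out too wide and the test rejects less often than its nominal level. At stake is a little precision on the primary endpoint, and an analysis that does not follow the randomisation.

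**Working it through.** **1. Is the allocation stratified by centre?** 15 × 30 + 18 = 468 = 3 × 156, so the 16 blocks make up the whole trial. Each block is used by one centre only, and a centre receives another after completing its own. Every completed block of 30 adds 10/10/10 to its centre, and the last adds 6/6/6. So yes, with exact balance in completed blocks; only a block left unfinished can upset it.

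**2. The plan's own sample size.** Inputs from section 8.1: difference 2 days; SD 5.87499 (common practice) and 4.80257 (PCT arm); alpha 0.025, taken as two-sided because that reproduces the stated figure; power 80%.

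- Pooled SD = √((5.87499² + 4.80257²)/2) = 5.366
- Normal approximation: 2 × (2.2414 + 0.8416)² × 5.366²/2² = 136.9, so 137 per group
- Noncentral t: 139 per group, the stated figure
- Mann-Whitney with efficiency 3/π: 145 per group by noncentral t (139 × π/3 = 145.6), against the stated 146

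The plan's figures therefore come from an analysis without centre, and they are sound for that analysis.

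**3. The cost of leaving centre out.** Let ρ be the share of within-arm variance in antibiotic days that lies between centres. The protocol does not give it, so the values below are assumptions. The centre shift is taken to be the same in both arms, and 5.366 is taken as the total SD. With arms balanced within centre:

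- SE the one-way test reports ≈ σ√(2/n); true SE = σ√((1−ρ)·2/n)
- True type I error = 2[1 − Φ(2.2414/√(1−ρ))]
- Relative CI width = 1/√(1−ρ)
- Power without centre = Φ((0.3727√(n/2) − 2.2414)/√(1−ρ))
- Power with centre = Φ(0.3727√(n/2)/√(1−ρ) − 2.2414)

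Here 0.3727 = 2/5.366. At n = 156, 0.3727 × √78 = 3.292, and 3.292 − 2.2414 = 1.051.

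- ρ = 0.05: without centre Φ(1.051/0.9747) = 85.9%; with centre Φ(3.292/0.9747 − 2.2414) = 87.2%
- ρ = 0.10: without centre Φ(1.051/0.9487) = 86.6%; with centre Φ(3.292/0.9487 − 2.2414) = 89.0%

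| ρ (assumed) | Between-centre SD, 5.366√ρ | True type I error, no centre | CI wider by | Power at 156, without / with centre | Power at 146, without / with centre |
|---|---|---|---|---|---|
| 0 | 0 days | 0.0250 | 0% | 85.3 / 85.3% | 82.7 / 82.7% |
| 0.05 | 1.20 days | 0.0215 | 2.6% | 85.9 / 87.2% | 83.3 / 84.8% |
| 0.10 | 1.70 days | 0.0181 | 5.4% | 86.6 / 89.0% | 84.0 / 86.8% |

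**4. Check by simulation.** Three centres, 156 per arm balanced within centre, normal outcome, 6,000 runs per setting. At ρ = 0.10, power was 85.9% for the t test and 88.3% with a centre term; it was 84.5% for Mann-Whitney and 86.5% for van Elteren. Type I error was 0.018 without centre and 0.024 with it, for both pairs. At ρ = 0.05 the t test pair gave power 85.5% and 87.1%. The null rates there, 0.0248 and 0.0293, have the expected order. Both lie about two Monte Carlo standard errors or less above their theoretical values (√(0.025 × 0.975/6000) = 0.0020), so the 0.0215 rests on the formula.

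**The case against.** The strongest reply is that this is loose wording with little behind it. Much of it stands. The protocol reports no centre effect, so a loss of precision cannot be shown from it. Its treatment rules also limit how far centres can diverge: control patients have a 7-day default, although the physician may extend it (5.2), and both biomarker arms use the same thresholds at every site (5.3, 5.4). The omission errs only on the conservative side. The stated sample size never relied on adjustment. What the reply does not remove is that 6.2 and 8.2 describe the design wrongly, and that the tests the protocol does fix leave out the factor it randomises by.

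A reader might be tempted to go further in three ways, none of which the document supports.

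- *That the denial of stratification contradicts other sections.* Section 8.4.1 says: "Sub-group analyses will be performed on patients with severe CAP according to the CURB criteria and patients with non-severe CAP". Planning subgroups on severity does not imply that severity had to be a randomisation stratum; subgroups need no stratified allocation.
- *That the result could steer the model.* Section 8.4.3 says: "Possible confounders (e.g. co-morbidities, type of pathogen etc.) will be assessed", with correction where appropriate. The wording is open-ended, but nothing there replaces the primary test, which 4.4 and 8.1 fix as unadjusted. A covariate list may also stand in a statistical analysis plan that is not shown.
- *That adjustment is worth 156/(1−ρ) patients*, which is 164 or 173 per group at 5% or 10%, with power rising from 85.3% to 87.2% or 89.0%. That comparison sets the adjusted analysis against an estimator carrying the full variance. Balance within centre has already lowered the true variance, so the right starting points are 85.9% and 86.6%. The gains are 1.3 and 2.4 points, not 1.9 and 3.7.

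**Conclusion.** The point holds as a mismatch between design, description and analysis, with a small and conditional cost. Randomisation is stratified by centre in effect, the protocol says it is not, and no specified analysis includes centre.

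The primary tests are not invalid, and the trial is not underpowered because of this. Under an assumed 5-10% share of variance between centres, the price is roughly 1-3 points of power, intervals about 3-5% too wide and a type I error of about 0.022-0.018 in place of 0.025. That share would mean centres differing with an SD of about 1.2-1.7 days in both arms, which the reader can judge against a 7-day default. At a share of zero the price is practically nil. The figures also assume that blocks are completed. The change is worth making because it costs almost nothing, not because the present analysis would mislead.

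**What to change.** - In 6.2 and 8.2, replace the no-stratification sentence with a statement that randomisation is stratified by centre through centre-specific permuted blocks.
- In 4.4 and 8.1, include centre in the primary comparison: a centre term in the ANOVA or linear model on the normal branch, and a centre-stratified van Elteren test in place of each Mann-Whitney test on the other. The Holm correction applies as before.
- Optionally, name baseline CURB-65 as a prespecified covariate in the linear model. It is not a randomisation factor, so this is a separate choice made for precision.

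The cost is wording and a little programming; the analyst should confirm that the software named in 8.4.1 can run the stratified rank test. Centre is known for every patient and CURB-65 is already recorded on day 1 (6.4.1). No extra data, patients or procedures are needed, and the planned sample size stays as it is. Because the trial is open-label, the change should be fixed before outcomes are compared by arm.
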